### Exclusion criteria

Patients will be excluded from the study if they meet any of the following criteria: (1) documented evidence of moderate to severe TBI; (2) current alcohol or substance dependence within the last 6 months; (3) preexisting cognitive impairment as determined by a score greater than 3.3 on the short form of the Informant Questionnaire of Cognitive Decline in the Elderly [12, 31]; (4) neurological history other than TBI (for example, premorbid epilepsy, multiple sclerosis, Alzheimer’s disease); (5) history of schizophrenia, psychotic disorder, or suicidal intent; and (6) inability to provide a telephone number and a stable address.

### Procedures

Written informed consent will be obtained from all study participants prior to study enrollment. Participants will be screened for mild TBI, preexisting cognitive impairment, alcohol and substance dependence, and cognitive deficits in executive functioning. Those that pass the screening phase will be asked to complete a baseline assessment (6 weeks after hospital discharge) and follow-up assessments at 4 and 7 months following hospitalization. Table 1 summarizes the data collection procedures across the baseline and follow-up time points. Assessments will consist of cognitive tests and questionnaires that measure cognitive functioning, functional status, and depressive and PTSD symptoms. Patients will also be asked to answer demographic and health questions at the baseline assessment. Clinical characteristics will be extracted from the medical record. All data will be entered into the Research Electronic Data Capture system (REDCap, a secure, web-based application designed exclusively to support data capture) [32].

**Table 1 Tab1:** Data collection schedule after hospital discharge

	6 weeks	4 months	7 months
Patient characteristics			
Age, gender	x		
Race/ethnicity	x		
Marital status	x		
Educational level	x		
Insurance status	x		
Height/weight	x		
Smoking status	x		
Working status	x		
Comorbid conditions	x		
Recovery expectations	x		
Clinical characteristics			
Glasgow Coma Scale	x		
Injury Severity Score	x		
Mechanism of injury	x		
Type of injury	x		
Surgical procedure	x		
Length of hospital stay	x		
Intensive care unit stay	x		
Ventilator days	x	x	x
Medications	x	x	x
Complications	x	x	x
Executive functioning			
D-KEFS Tower Test	x	x	x
Trails B	x	x	x
FAS test	x	x	x
SART	x	x	x
Hotel Task	x	x	x
Dysexecutive Questionnaire	x	X	x
Cognitive Failures Questionnaire	x	x	X
Functional status			
Functional Activities Questionnaire	x	x	x
Quality of Life After Brain Injury	x	x	x
Psychological			
Patient Health Questionnaire-9	x	x	x
PTSD Checklist - Civilian Version	x	x	x

*D-KEFS* Delis-Kaplan Executive Function System, *SART* Sustained Attention to Response Test, *PTSD* posttraumatic stress disorder

### Randomization

Participants will be randomized to one of the three groups (telephone-based GMT, telephone-based education, usual care) in a 1:1:1 ratio. Block size will be determined randomly with the patient as the unit of randomization. A randomization list will be computer generated and administered thought the REDCap system. Randomization will occur immediately after the baseline assessment at 6 weeks. Surgeons and research personnel conducting the assessments will be unaware of group assignment.

### Interventions

#### Telephone-based GMT

The telephone-based GMT program will include seven sessions delivered by a physical therapist (Table 2). GMT was originally conceptualized by Robertson [33] and derived from Duncan’s [34] theory of goal neglect. Levine and colleagues expanded on GMT and tested a standardized protocol and treatment manual in patients with moderate to severe brain injury and in older adults with cognitive impairment [23, 35, 36, 21]. The GMT intervention targets cognitive deficits in executive functioning that impact a person’s ability to carry out daily tasks. This current study has adapted the GMT intervention to include mindfulness techniques [37] and to be delivered over the telephone, in collaboration with [name]. The first session is 1 h and conducted in-person to provide participants with a session-by-session treatment manual. The remaining six sessions are 30 min and are conducted once a week over the phone. Sessions focus on increasing awareness of one’s thoughts and experiences and increasing self-efficacy. Participants learn how to use mindful attention and goal setting to recognize and stop ‘absentmindedness’ and ‘automatic pilot’ in order to reduce daily errors and ‘slips’ (Fig. 2). Each session builds upon the content of the previous session. Weekly homework is personally tailored based on patient goals.

**Table 2 Tab2:** Summary of goal management training intervention by session

Session 1: Slip-ups	Overall introduction, define goals and absentminded slips, raise awareness of consequences of slips, introduce present-mindedness and mindful practice in daily life
Session 2: Stop the automatic pilot	Define automatic pilot and how it leads to errors, learn how to ‘STOP’ automatic pilot, practice present-mindedness
Session 3: The mental blackboard	Define the mental blackboard, learn how to ‘STOP’ and check mental blackboard, staying in the present through breathing
Session 4: State your goals	Define goals, learn how to state goals, practice ‘STOP’ and ‘STATE’ and breath focus to become present-minded
Session 5: Making decisions	Define competing goals, learn how to understand emotional reaction to indecision, practice ‘STOP-STATE’ to reduce stress and indecision
Session 6: Splitting tasks into subtasks	Define overwhelming goals, learn how to split goals, practice ‘STOP-STATE-SPLIT’
Session 7: Checking (STOP)	Learn how to recognize errors in ‘STOP-STATE-SPLIT’ cycle, review how to use ‘STOP’ to monitor daily tasks, review strategies for being present-minded, wrap-up

**Figure 2 Fig2:**
[figure not shown]
Goal management training overview

#### Telephone-based education

The telephone-based education group will receive an educational program that is matched to the GMT intervention in terms of session length and contact with the study therapist. The education program includes seven sessions delivered by a physical therapist (Table 3). Material was developed by Levine *et al*. [23] based on material commonly employed in rehabilitation centers and has been successfully used in several studies as a comparison to the GMT intervention [35, 38]. Sessions address education on brain function and cognitive principles of memory, attention, language, perception, and motor skills. Education on stress reduction, sleep hygiene, energy management, exercise, communication, and nutrition are also provided. The first session is conducted in-person to provide participants with a session-by-session treatment manual. The remaining six sessions are conducted once a week over the phone.

**Table 3 Tab3:** Summary of education intervention by session

Session 1: Introduction	Overall introduction, explain the goals of the program, define basic brain anatomy and consequences of trauma
Session 2: Brain activity	Explain importance of keeping brain active, define the assessment of brain activity
Session 3: Memory I	Explain the importance of memory, define the types of memory and memory processes
Session 4: Memory II	Review memory and the brain, learn how memory breaks down, define functional implications of memory loss
Session 5: Attention and executive function	Define attention and executive functioning, learn how attention and executive functioning breaks down
Session 6: Lifestyle I	Explain importance of stress, sleep, and exercise on brain function, define the influence of lifestyle on recovery
Session 7: Lifestyle II	Explain importance of nutrition, energy management, and communication on brain function, review healthy lifestyle for recovery, wrap-up

#### Usual care

Participants in the usual care group will receive usual care as determined by the treating surgeon. Usual care may include referral to a physical therapist, occupational therapist, psychiatrist, and/or psychologist. At the end of the intervention phase, participants will be asked whether they had, on their own initiative, followed a course to improve their cognitive functioning.

### Quality assurance

One study physical therapist will complete training in both the GMT and education programs. Formal training will occur with the principal investigator (PI) of the study ([name]) and an experienced neuropsychologist ([name]). Written and skills competency tests will be completed at the end of training. After passing both tests (scores >85), the GMT and education treatments will be implemented with study staff and a pretest of both programs will occur with one patient. All sessions during the pretest will be audiotaped and reviewed to evaluate adherence to the treatment protocol and structured manual.

Our treatment integrity protocol includes detailed session-by-session treatment manuals for the telephone-based groups and ongoing supervision to ensure accurate and consistent treatment delivery (provided via weekly clinical team meetings). The study physical therapist’s adherence to procedures will be assessed by audio recording all sessions and randomly selecting sessions for the investigators to review using standardized fidelity checklists. The study physical therapist will also complete a checklist of all the components delivered during each session and make note of any protocol deviations. If the integrity of the treatments is compromised, the study therapist will be retrained and 100 % of audiotapes will be reviewed until problems are addressed.

### Primary outcome measures

#### Executive functioning

Executive functioning will be measured using a battery of widely used and previously validated cognitive tests and patient-reported questionnaires (Table 4).

**Table 4 Tab4:** Cognitive tests and patient-reported questionnaires for assessing executive functioning

Test	Description	Executive function	Outcome	Scoring	Interpretation
DKEFs Tower Test [30]	A timed test that involves constructing towers of discs on a set of pegs with rules for movement and setup	Planning, sustained attention	Total number of moves	Age-adjusted scaled score [range: 1 to 19]	Higher scaled scores indicate better performance
					Scaled scores ≤7 indicate significant impairment
Trails B [30, 39–41]	A timed test that involves drawing a line between a series of alternating numbers and letters	Attentional control, cognitive flexibility, set shifting	Total time	Age, education, and sex-adjusted T-score	Higher T-scores indicate better performance
					T-scores ≤35 indicate significant impairment
FAS [13]	A timed test that involves generating as many words beginning with the letters F, A, and S	Verbal fluency	Total number of words	Age, education, and sex-adjusted T-score	Higher T-scores indicate better performance
					T-scores ≤35 indicate significant impairment
SART [44–47]	A timed computer test that involves a go/no-go task using single-digit numbers	Sustained attention and inhibition	Errors of commission and omission, reaction time	Sum of errors Reaction time	Higher number of errors and slower reaction time indicate poorer performance
Hotel Task [48, 49]	A timed test that involves a real-life multitasking situation with different task components	Planning, organization	Total time, time spent on each task, number of tasks attempted	Deviation time from optimal time allocation	Greater deviation time indicates poorer performance
DEX [50, 52]	A 20-item questionnaire that measures behavioral change and difficulties with executive functions	Changes in emotion, personality, motivation, behavior, and cognition	Total score	Summed score [range: 0 to 80]	Higher scores indicate greater cognitive impairment
CFQ [51, 53, 54]	A 25-item questionnaire that measures daily mental errors related to attention and cognition	General everyday life cognitive failures	Total score	Summed score [range: 0 to 100]	Higher scores indicate greater cognitive impairment Scores >38 indicate cognitive difficulties

*D-KEFS* Delis-Kaplan Executive Function System, *SART* Sustained Attention to Response Test, *DEX* Dysexecutive Questionnaire, *CFQ* Cognitive Failures Questionnaire

The D-KEFS Tower Test assesses the ability to plan and strategize efficiently and requires participants to move discs across three pegs until a tower is built using the fewest number of moves possible [30]. D-KEFS Tower Test is timed, but participants are unaware of specific time constraints. If the tower is not built within the allotted time, participants receive a score of 0. Completed D-KEFS Tower Test scores are adjusted for age and converted into a scaled score that ranges from 1 to 19, with higher scores reflecting better performance. The D-FEKS Tower Test has demonstrated moderate correlations with self-reported executive functioning and has been found to be sensitive and specific for brain lesion diagnosis [30].

Trails B is a time-based test that measures set shifting and cognitive flexibility [30]. Participants are asked to draw a line between a series of alternating numbers and letters according to a specified sequence. Trails B has acceptable test-retest reliability [39] and good convergent and predictive validity with significant associations with self-reported executive functioning and functional status in patients with TBI and older adults [40, 41]. The FAS assesses verbal (letter) fluency and is a valid and sensitivity measure of frontal lobe function [13]. Participants are given 1 min to generate as many words as they can for each of the letters F, A, and S. The FAS exhibits moderate correlation with measures of executive functioning after TBI and good sensitivity and specificity for patients with dementia [42, 43]. Trails B and FAS scores are adjusted for age, education, and gender and converted to T-scores, with a norm referenced mean of 50.

The Sustained Attention to Response Test (SART) is a go/no-go computer test that identifies failures of sustained attention [44]. Participants are instructed to respond to randomly presented single numbers (one through nine) every 1.15 s, except for a single no-go number (for example ‘three’). The number of errors (commission and omission) and reaction time are recorded and used as scores for the SART. The SART has good sensitivity at discriminating attention error rates of TBI patients [45, 46] and good convergent validity through associations with self- and informant-reported measures of everyday attention failure and lapses [46, 47].

The Hotel Task is a measure of planning and organizational ability and involves the participant modeling a real-life multitasking situation as a hotel manager [48]. The participant is asked to try and complete five different tasks: compiling bills; sorting a charity collection; looking up telephone numbers; sorting conference labels; proofreading the hotel leaflet. In order to complete all five tasks, the participants must distribute their time equally across the total 15-min allotment (that is, 3 min per task). Scoring of the Hotel Task is the total deviation from optimal time allocation. The Hotel Task is a sensitive measure for detecting frontal dysfunction in various conditions [48, 49].

Patient-reported executive functioning will be measured using the Dysexecutive Questionnaire (DEX) [50] and the Cognitive Failures Questionnaire (CFQ) [51]. The DEX is a 20-item questionnaire that assesses behavioral changes in executive functioning related to the areas of inhibition, memory, intention, and affect. Items on the DEX are scored using a 5-point Likert scale ranging from 0 (never) to 4 (very often) with total scores ranging from 0 to 80. The DEX has demonstrated good internal consistency and moderate correlations with other measures of patient-reported executive functioning in adults with dementia [52]. The CFQ is a 25-item questionnaire that assesses daily mental errors associated with distractibility, blunders, names, and memory [51]. Items on the CFQ are scored using a 5-point Likert scale ranging from 0 (never) to 4 (very often) with total scores ranging from 0 to 100. CFQ scores greater than 38 have been reported to indicate persistent cognitive difficulties [53]. The CFQ has been shown to have excellent psychometric properties and moderate to high correlations with cognitive tests and questionnaires in patients following head injury [54].

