## Abstract

**Background:**

Approximately 1 million individuals experience a mild traumatic brain injury (TBI) and cost the United States nearly $17 billion each year. Many trauma survivors with mild TBI have debilitating and long-term physical, emotional, and cognitive impairments that are unrecognized at trauma centers. Early intervention studies are needed to address these impairments, especially cognitive deficits in executive functioning. Goal management training (GMT) is a structured cognitive rehabilitation program that has been found to improve executive functioning in patients with moderate to severe TBI. The current study adapted the GMT program for telephone delivery in order to improve the accessibility of rehabilitation services in a patient population with multiple barriers to care and significant yet unrecognized cognitive impairment. The primary objective of this study is to examine the efficacy of telephone-based GMT for improving executive functioning, functional status, and psychological health in trauma survivors with mild TBI.

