The purpose of this study is to examine the efficacy of a telephone-based GMT program for improving executive functioning, functional status, and depressive and PTSD symptoms in trauma survivors with mild TBI. The GMT program will be compared to a telephone-based education program and usual care at 4 months (treatment completion) and 7 months following hospital discharge. Emerging research suggests that telephone rehabilitation may be a feasible and effective alternative (with much broader applicability) to clinic-based interventions [24–27]. Researchers have also suggested that rehabilitation conducted in a patient’s well-known and natural environment may facilitate and enhance the transfer of skills to the everyday living setting [28].

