### Data analysis

All data will be explored numerically and graphically for normality and appropriateness of parametric statistical testing. Analyses will be conducted using models with either original data or suitably transformed data (for example, log-linear transformation) or nonparametric analyses if necessary. Baseline variables will be summarized using appropriate descriptive statistics and compared across groups. The characteristics of the patients who are lost to follow-up will be compared to those who complete the follow-up assessments. For each outcome, we will perform longitudinal mixed-effects regression analyses, with a random intercept for patient to account for the correlation among observations from the same patient. We will examine possible nonlinear effects of the treatment over time. A random slope over time may be included to allow a separate slope to be estimated for each patient. We will fit the model with an independent conditional covariance structure and an autoregressive structure and choose the best data-supported model based on the deviance information criteria or a related criterion. The primary analysis will be intent-to-treat; missing observations due to dropout and other reasons not related to the treatments will be handled with multiple imputation methodology [64]. Statistical significance will be *P* <0.05. All analyses and reporting will be consistent with Consolidated Standards of Reporting Trials (CONSORT) guidelines. The data analysis plan will be fully specified and approved prior to completion of data collection.

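### The primary outcome is a seven-instrument battery judged outcome by outcome at P<0.05, with no lead outcome, comparator, time point or success rule, so the error rate for a primary claim is well above 5%

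*Protocol article*

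**What the plan says.** - **Primary outcome.** Under Primary outcome measures, the Executive functioning subsection states "Executive functioning will be measured using a battery of widely used and previously validated cognitive tests and patient-reported questionnaires (Table 4". Table 4 lists the D-KEFS Tower Test, Trails B, FAS, SART, Hotel Task, DEX and CFQ. None is marked as the lead, and no composite is defined.
- **Scores within the battery.** For the SART, "The number of errors (commission and omission) and reaction time are recorded and used as scores for the SART". Table 4's scoring column gives it a sum of errors and a reaction time.
- **Comparisons.** The Background says "The GMT program will be compared to a telephone-based education program and usual care at 4 months (treatment completion) and 7 months" after discharge. Neither the comparators nor the times are ranked.
- **Analysis.** Data analysis says "For each outcome, we will perform longitudinal mixed-effects regression analyses, with a random intercept for patient", and "Statistical significance will be *P* <0.05". It also promises a fully specified analysis plan before data collection ends.
- **Objective.** The abstract says "The primary objective of this study is to examine the efficacy of telephone-based GMT for improving executive functioning, functional status, and psychological health". The body places functional status and psychological health under Secondary outcome measures.
- **Status.** Recruitment was complete in February 2015, and the trial is reported as being in follow-up.

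**The concern.** The article presents the study as an efficacy trial. An efficacy claim needs a known chance of being made when the treatment does nothing. Here the primary hypothesis is spread over seven or more scores, two comparators and two visits, and the only threshold given is the one for a single test. The Sample size section follows the same logic. It counts credible intervals excluding zero separately for each response variable, sets no joint criterion, and gives detectable effects for five of the seven primary instruments (not the SART or the Hotel Task).

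Two things are at stake. One nominally significant score, against one control, at one visit, could be reported as a primary finding although such a result is common by chance. And a mixed battery, for example Trails B better, FAS unchanged and CFQ worse, has no pre-set reading.

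**Working it through.** **The plan's own figure.** The article states no error rate for the primary family, so there is none to reproduce. Its power statement gives no power value and no SDs and rests on pilot data that are not shown, so it cannot be checked either.

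**Inputs from the article**
- Scores K: 7 (one per instrument), 8 (Table 4 scoring column) or 9 (SART errors split).
- Contrasts: 2 (GMT vs education, GMT vs usual care). Follow-up visits: 2.
- Threshold: P<0.05 per test. Sidedness is not stated; two-sided is assumed.
- Allocation 1:1:1. With n per arm and common variance σ², each difference has variance 2σ²/n and the two share covariance σ²/n through the GMT arm. Their correlation is (σ²/n)/(2σ²/n) = 0.5.

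**Assumed, because the article gives no values**
- Correlation between outcomes: 0 to 0.7.
- Correlation between visits: 0.6.

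**Number of tests.** K × 2 × 2 = 28, 32 or 36 if both contrasts are tested at both visits. K × 2 = 14, 16 or 18 with one test per outcome and contrast.

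**Upper reference, independent tests.** 1 − 0.95^k gives:
- k = 7: 30.2%
- k = 9: 37.0%
- k = 14: 51.2%
- k = 28: 76.2%
- k = 36: 84.2%

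**With correlation.** Z-statistics were drawn from a multivariate normal under no effect (400,000 draws). The correlation matrix is the product of the outcome, visit and contrast correlations, and scores are signed so that higher is better. Either direction means any |Z| > 1.96. Favouring GMT means any Z > 1.96. Each cell shows either direction / favouring GMT.

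| Design | K | r = 0 | r = 0.3 | r = 0.5 | r = 0.7 |
|---|---|---|---|---|---|
| 2 contrasts × 2 visits | 7 | 69% / 43% | 65% / 36% | 57% / 30% | 47% / 24% |
| | 8 | 74% / 48% | 69% / 39% | 61% / 33% | 50% / 26% |
| | 9 | 78% / 52% | 73% / 42% | 64% / 35% | 52% / 27% |
| 2 contrasts, one test each | 7 | 49% / 28% | 44% / 23% | 38% / 20% | 30% / 15% |
| | 8 | 53% / 31% | 48% / 25% | 41% / 21% | 32% / 16% |
| | 9 | 58% / 34% | 52% / 28% | 44% / 23% | 34% / 17% |

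Here r is the correlation between outcomes. A single pre-named two-sided test would give 5% / 2.5%. Naming one contrast and one time but keeping the whole battery still gives 18-37% in either direction.

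**Effect of a composite on precision.** The SD of the mean of k standardised scores is √((1 + (k − 1)r)/k).
- k = 3: √(1.6/3) = 0.73 at r = 0.3, and √(2.4/3) = 0.89 at r = 0.7.
- k = 5: √(2.2/5) = 0.66 at r = 0.3, and √(3.8/5) = 0.87 at r = 0.7.

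**The case against.** **The analysis plan may deal with it.** The article promises a full plan, and adjustment methods, contrast order and testing sequence commonly sit there. This stands in part: one cannot conclude that the trial has no error control. But choosing what is primary is the protocol's task. The protocol has made that choice, seven instruments on an equal footing, and attached a single-test threshold to it.

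**Separate tests at each visit are not specified.** This also stands. Data analysis describes one longitudinal model per outcome, and the two visits come from the comparison described in the Background. So 28 tests is not a floor, which is why the one-test-per-contrast rows are shown. They remain far above 5%.

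**A reader might infer that a false efficacy claim is more likely than not.** The working does not support that. Rates above 50% mostly count differences in either direction, including those favouring a control. In favour of GMT, 50% is passed only with nine mutually uncorrelated scores tested at both visits. Zero correlation is an outer bound, since the outcome section itself reports moderate correlations of several of these measures with other executive or cognitive measures.

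**A reader might also infer a rule that any one significant test proves efficacy.** The article states no such rule. The fault is that it states no success rule at all.

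**The abstract mismatch is small.** The body separates primary from secondary measures clearly, and the Background gives the same broad purpose as the abstract. It still needs correcting, because calling all three domains the primary objective invites a wider primary claim.

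**Conclusion.** The concern holds in this form: the protocol fixes a multi-score primary outcome, two unranked comparators and two unranked times, with P<0.05 applied per outcome and no success rule. Taken as written, the chance of at least one nominal primary result under no effect is about 47-78% in either direction and 24-52% in favour of GMT if both visits are tested (about 30-42% in favour at outcome correlations of 0.3-0.5). It is about 30-58% and 15-34% with one test per outcome and contrast. These figures rest on assumed correlations between outcomes (0-0.7) and visits (0.6), on the 0.5 that follows from the shared GMT arm, and on two-sided tests. The exact size is uncertain, but every scenario is several times the nominal rate. An analysis plan not seen here could still add adjustment.

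**What to change.** Before any outcome is seen by arm, amend Primary outcome measures and Data analysis in one of two ways:

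1. **One primary test.** Name one score or composite, one comparator and one time point. Put the other contrasts and times in a fixed sequence, or label them supportive and report them with intervals.
2. **Holm over the primary family.** List every score, contrast and time in the family, and state that an efficacy claim needs an adjusted P<0.05. The smallest P would face 0.05/28 = 0.0018 with seven scores, or 0.05/36 = 0.0014 with nine, if both visits are tested.

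In either case, reword the abstract's primary objective to match the body's split into primary and secondary outcomes.

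The cost is wording only. The assessments already scheduled suffice, and the article reports follow-up as still under way, so no new data are needed. The downside is that claims on single tests become harder. A composite offsets this only in part: its SD relative to one standardised score is 0.73-0.89 with three tests and 0.66-0.87 with five, at correlations of 0.3-0.7, and the gain assumes similar standardised effects on each component.
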